### Data analysis plan

Study data will have a three-level nested structure: clients within therapists, within sites (we will average across sessions for each client). The analytic approach for these nested data will be multilevel mixed-effects models examining the effects of Condition and Phase on dependent variables aggregated across each time period: 4-month Baseline phase (prior to Core Training) and 12-month Implementation phase. We will use maximum likelihood estimation for continuous variables and robust weighted least squares for categorical variables. We will model Site and Therapist as random effects in all models. We will include Site (census, location, organizational context), Therapist (age, sex, ethnicity, experience, EBI attitudes, family therapy proficiency), and Client (age, sex, race/ethnicity, family composition) factors at their respective levels to examine potential covariance effects. Variables representing adherence to Core Training and adherence to Facilitation will be entered at the Site level to ensure that fidelity differences do not confound experimental comparisons; these factors will also be tested as potential moderator variables. Effect sizes will be calculated using the standardized *d* effect size indicator, interpreted as the standardized difference between contrasts: between Conditions (Core Training vs. Core + Facilitation) and Phase (Baseline vs. Implementation) [42].

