## Methods/design

### Study design

The study design is a two-group, parallel cluster randomized trial with baseline comparison: following a 4-month Baseline phase, ten ASU treatment sites will be randomized across two conditions, Core Training versus Core + Facilitation, for a 1-year Implementation phase. Cluster randomized trials are appropriate when interventions are allocated randomly to organizational units (in this case, treatment sites) rather than to individuals to enhance ecological validity [42]. For aims 1 and 2, we will collect FBS quality data along with MTFS-I uptake data. For aim 3, we will extract client outcome data from archived state databases for 1-year pre-Implementation (prior to Core Training activities) and 1-year follow-up. In aim 1, by comparing Baseline versus Implementation phases, we can examine the effectiveness of the Core Training strategy for enhancing FBS quality across all study sites, thereby yielding proof-of-concept data in accord with the well-established stage model of behavioral treatment development [43]. In aims 2 and 3, by experimentally comparing Core + Facilitation versus Core Training, we can test the value of additional time and resource expenditures embodied in Facilitation procedures for maximizing intervention benefits in FBS quality and client outcome, in line with established principles of facilitating system-level behavioral interventions [37].

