### Study sites, sample size, and randomization procedures

Ten outpatient ASU treatment sites will be purposively sampled to promote site diversity in size and location. Based on these factors, along with data on organizational characteristics of selected sites (see below), we will create yoked pairs for randomization so that each pair is matched as closely as possible (e.g., sites that are both small, rural, and with a single clinical supervisor). Randomization to Core Training or Core + Facilitation will occur after each pair has completed Core Training. State census data indicate that the median annual enrollment across substance use programs serving youth age 13–21 years is about 120. Thus for aim 3 analyses of archived state data, the study will include approximately 1200 clients across ten clinics. For aim 2, we expect to enroll 80 therapists total (8 therapists per site [6 active slots plus 2 to replace dropouts]) treating 480 total cases (60 therapist slots × 8 cases/year) for which ITT-ABP data will be provided. We anticipate that treatment will average ~ 6 sessions/case, yielding 2880 submitted fidelity checklists. For observational fidelity analyses, therapists at each site will submit audio-recorded sessions with consenting families; conservatively, about half of study families (*n* ~ 240) will consent to allow recording, and about half of sessions with completed fidelity checklists will have a companion recording, yielding a final pool of *n* ~ 721 recordings. See Fig. 1 for a CONSORT flow chart of projected study enrollment. See Fig. 2 for an outline of the components of the MTFS-I learning system, along with the two implementation strategies (Core Training, Facilitation), all of which are described in detail below.

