### Study measures

The ITT-ABP collects post-session therapist-report data on family participation in treatment activities (clinical assessments, treatment planning meetings, therapy sessions) and therapist use of core family therapy techniques [19]: family engagement and goal setting, relational reframing, family skills building, and coaching family interactions. It requires 2–3 min to complete and has demonstrated construct validity [15], concordance with observational ratings [16], benchmark validity for community therapists [17], and predictive validity for multiple client outcomes [55]. Client outcome data will be extracted from a state-regulated management information system used to track all client episodes of care in licensed substance use treatment programs with regard to achievement of therapeutic goals and reduction of substance use. Baseline covariates will be assessed via three therapist-report measures. *Organizational Social Context* measure [56] yields scaled scores that can be compared to national norms describing the organizational context of behavioral health clinics with regard to Organizational Culture, Organizational Climate, and Work Attitudes [57]. *Evidence-Based Practice Attitude Scale* [58] is a 15-item measure of clinician attitudes regarding the appeal of EBIs, required use of EBIs, openness to trying EBIs, and unfavorable attitudes toward EBIs [58, 59]. *Therapist Self-Reported EBI Proficiency* [15] averages therapists’ own judgments about their degree of allegiance to, and their perceived technical skill in, multiple EBIs including family therapy.

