### Power analysis

With cluster trials, power is substantially affected by the number of sites and clusters (i.e., therapists) within site, and minimally by clients within cluster [42]. For aim 2 (therapist-report fidelity data), in which the unit of analysis is ITT-ABP checklists (*n* = 2880), using an effect size of 0.50 for paired contrasts between conditions, with 5 sites per comparison and 48 clients within each site, and with moderately sized intraclass correlations at levels 2 and 3 (*ρ* = 0.05) [60], yielded power of approximately 0.80*.* Our recent fidelity study [17] found the mean Family Therapy fidelity score for community therapists (2.4; SD = 0.63) was significantly higher than that for research therapists (2.0/.35). Using the standard deviation of Family Therapy fidelity scores produced by community therapists (a sample similar to the current study) and an effect size of 0.45 yields a product of 0.28, a threshold indicating meaningful change in fidelity (as illustrated by the difference found between community versus research therapist scores) that would yield a significant effect with power = 0.80. For aim 3 (archived outcome data), in which the unit of analysis is the client, for 1200 clients and assuming 10 sites and 80 therapists, an effect size of *δ* = 0.50 in line with that found similar implementation studies (e.g., [61]) yielded power = 0.80.

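### Five site-level terms beside Condition leave 3 site degrees of freedom for a between-site test, while the stated power rests on a plain 5-versus-5 comparison with 8

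*Protocol article*

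**What the plan says.** Under Study design, "ten ASU treatment sites will be randomized across two conditions". Under Study sites, sample size, and randomization procedures, "we will create yoked pairs for randomization so that each pair is matched as closely as possible", using size, location and organizational characteristics.

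The Power analysis describes the aim 2 structure in these terms: "with 5 sites per comparison and 48 clients within each site". It takes d = 0.50 and sets the intraclass correlations for therapist and site at 0.05. The calculation is for data "in which the unit of analysis is ITT-ABP checklists" (2880 of them), and the stated power is about 0.80. The section mentions no covariates, no variance explained by covariates and no loss of degrees of freedom.

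The Data analysis plan makes Site and Therapist random in all models and averages sessions within client. On covariates it says: "We will include Site (census, location, organizational context), Therapist (age, sex, ethnicity, experience, EBI attitudes, family therapy proficiency), and Client" factors. Its next sentence adds adherence to Core Training and adherence to Facilitation as site-level variables. Study measures describes the organizational instrument as "describing the organizational context of behavioral health clinics with regard to Organizational Culture, Organizational Climate, and Work Attitudes", which is three domains.

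**The concern.** Site is the randomised unit and a random effect, so a Condition contrast made between sites is judged against variation among ten sites. Each site-level term takes one of the few degrees of freedom available for that judgement. It also raises the variance of the Condition estimate to the extent that the term is correlated with Condition by chance.

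The model described is therefore not the one that was sized. The contrasts most clearly exposed are completion of online training and review of feedback reports. These parts of the aim 2 uptake hypothesis occur only in the Implementation phase and have no baseline counterpart. The aim 2 Condition effect on fidelity is exposed if it is tested as a main effect. A valid test loses power. A large-sample test after maximum likelihood does not register the lost degrees of freedom, and gives more false positives instead.

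**Working it through.** **Inputs.** From Power analysis: d = 0.50, 5 sites per arm, intraclass correlation 0.05 for site and for therapist (residual 0.90), 2880/10 = 288 checklists per site, 48 clients per site. From Study sites, sample size, and randomization procedures: 6 active therapist slots per site. Assumed, because not stated for aim 2: two-sided alpha of 0.05.

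**Reproducing the plan's figure.**
- Checklists: site-mean variance = 0.05 + 0.05/6 + 0.90/288 = 0.0615. SE of the difference = √(2 × 0.0615/5) = 0.157. Noncentrality = 0.50/0.157 = 3.19. With t on 8 df, power is 0.797, which matches the stated 0.80.
- Client means, the unit in the Data analysis plan: 0.05 + 0.05/6 + 0.90/48 = 0.0771. SE = 0.176. Noncentrality = 2.85. With t on 8 df, power is 0.70.

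**Counting site terms.** Census, location and organizational context make three; the two adherence variables make five. Site df = 10 − 2 − 5 = 3. If the three organizational domains enter separately, the count is seven and 1 df remains.

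**Power with k site terms that explain no site variance.** Perfect balance uses the noncentral t with 8 − k df and the SE above. Chance imbalance comes from simulating 6,000 trials per setting: five pairs, one site of each pair randomised to each arm, site-mean regression with t on 8 − k df, and within-pair covariate correlation from 0 to 0.95. Each cell gives checklists / client means.

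| Site terms | df | Critical t | Perfect balance | Chance imbalance |
|---|---|---|---|---|
| 0 | 8 | 2.31 | 0.80 / 0.70 | – |
| 1 | 7 | 2.36 | 0.78 / 0.69 | 0.73–0.78 / 0.63–0.69 |
| 2 | 6 | 2.45 | 0.76 / 0.66 | 0.65–0.74 / 0.55–0.65 |
| 3 | 5 | 2.57 | 0.72 / 0.63 | 0.55–0.70 / 0.46–0.60 |
| 5 | 3 | 3.18 | 0.58 / 0.50 | 0.31–0.45 / 0.26–0.39 |
| 7 | 1 | 12.71 | 0.20 / 0.18 | not run |

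**If the terms explain half the site variance** (chance imbalance): three terms give 0.73–0.89 / 0.60–0.75, and five give 0.46–0.62 / 0.35–0.50. In both cases the upper end is the closely matched case.

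**The five-term rows are generous in one respect.** They treat all five terms as unrelated to Condition. Facilitation is delivered in one arm only, so adherence to it is tied to Condition. For illustration, a variance inflation factor of 5 would take the checklist figure at 3 df from 0.58 to 0.17.

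**Large-sample alternative.** On client means, with a maximum-likelihood variance (residual sum of squares/10, floored at the within-site part, 0.05/6 + 0.90/48 = 0.027) and a cut-off of 1.96, the false-positive rate is about 11% with no site terms and about 14–22% with five. The t test stays near 5% throughout.

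**The case against.** The strongest objections are these.

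- **The count.** The quoted sentence names three site factors. A reader might infer at least five baseline covariates by splitting organizational context into its domains. The Data analysis plan does not say that the domains enter separately, so that reading is not supported. The count of five rests on the two adherence variables in the next sentence.
- **The size.** A reader might also infer that the stated power cannot be reached. That is too strong. Under perfect balance, five terms explaining half the site variance would bring checklist power back to 0.78. Three closely matched factors explaining half of it cost little or nothing. Matching factors are presumably chosen as prognostic, so zero variance explained is the unfavourable end. However, the plan assumes no figure for it.
- **The test.** Checklists are collected in both phases and the plan includes Phase-by-Condition products. Site covariates that are constant over phases largely drop out of those terms, so a fidelity result tested that way is largely spared. The 0.80 was stated for fidelity data. No effect size or power is given for uptake, and uptake is recorded on staff, not on 48 clients per site. This stands.
- **Screening.** The stated aim of examining covariate effects could mean that not all terms are kept, and an article condenses. But the wording commits to including the terms, and no selection rule or limit is given.
- **Shared cause.** The 11% false-positive rate without covariates comes from having few sites. Only the increase to 14–22% belongs to this point.

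**Conclusion.** The concern holds for Condition contrasts made between sites. As written, five site terms leave 3 df against the 8 on which the power rests. Fewer remain if the organizational domains enter separately.

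If the five terms explain no site variance, power falls from 0.80 to about 0.58 on checklists, or from 0.70 to 0.50 on client means, under perfect balance. With chance imbalance it is about 0.3–0.45 or 0.26–0.39. With only the three baseline factors it is about 0.55–0.72 or 0.45–0.63.

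These figures rest on the plan's d and intraclass correlations, six therapists per site and two-sided 5%. For uptake the loss of degrees of freedom is certain wherever the contrast has no baseline counterpart. The power values there are illustrative, because d = 0.50 is borrowed. The change should be made, but the point does not show that every aim 2 test is underpowered.

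**What to change.** In the Data analysis plan:

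- Limit confirmatory between-site Condition models to at most one or two pre-named baseline site factors (census, for example), tested with small-sample site degrees of freedom.
- Keep the Therapist and Client baseline covariates.
- Move the remaining site factors and both adherence variables to models labelled exploratory.

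In the Power analysis, restate aim 2 power for the model and degrees of freedom actually used. Even one or two terms have a cost if they explain nothing, as the table shows.

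The cost is a few sentences and no new data. Chance site imbalance on the dropped factors would be handled by the matching and reported descriptively, not adjusted for. If matching is close and prognostic, the unadjusted test may be somewhat conservative: with within-pair correlation of 0.8–0.95 and half the site variance explained, its true size is about 0.026–0.032. The limit of one or two is a judgement from the table, not a figure in the documents.

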## Discussion

### Key study innovations

This study has several innovations that advance the science of ASU services research. MTFS-I is the first learning quality improvement system created to monitor non-manualized delivery of family therapy for ASU. MTFS-I leverages user-centered online training methods designed to strengthen the fidelity of FBS and also increase the accuracy with which therapists report on their own implementation of FBS. By increasing the capacity of therapists to report on their own FBS delivery, MTFS-I can significantly enhance the practicality and utility of methods for monitoring clinical service quality.

This study operationalizes FBS fidelity as a quality indicator for ASU treatment. Within the evolving behavioral healthcare system, quality indicators are the primary barometers used to assess the appropriateness and potential effectiveness of care [2]. Conventional quality indicators capture broad principles of care such as treatment selection, retention and follow-up rates, referrals for ancillary care, and client safety [5]. Quality indicators of this kind are important but limited: They can verify only if a given procedure occurred or a service quota was met, and not the degree of treatment fidelity delivered. In addition to tracking family participation in services, the current study also measures session-level extensiveness of treatment techniques as a quality indicator. This movement toward dimensional measurement of service quality in routine care is a top priority for improving quality procedures. For example, dimensional assessment of ASU quality affords greater specification of therapeutic processes; this, in turn, facilitates clinically rich decision-making tailored each client’s unique needs [63]. Moreover, this study employs observational methods to verify therapist self-reports of FBS technique use. Observational assessment of treatment practices is roundly needed to support data-driven upgrades to usual care [6, 22].

By focusing on core practice elements of the FBS approach, this study diverges markedly from conventional efforts to disseminate FBS for ASU via manualized family therapy models relying on purveyor-driven quality procedures. The manual-driven strategy has encountered barriers to implementing FBS models in routine care: high consultation costs, limited flexibility for selective treatment planning favored by clinicians, and sustainability limitations due to vicissitudes in local regulatory practices, purveyor commitment, and provider stamina to honor quality procedures [6, 27]. As previously discussed, the core elements approach can mitigate many of these barriers, and so far it has accumulated an impressive research base in comparison to disorder-specific treatment manuals and usual care for youth mental health problems [64, 65].

That being said, it is critical to note that MTFS-I is not intended to train therapists to implement new EBIs, nor to replace standard clinical training experiences for EBIs already in practice. As described above, MTFS-I focuses on training and feedback for EBIs that are already endorsed by, and perhaps practiced to some degree by, the given site. The goal is to promote more extensive and high-quality use of site-endorsed EBIs. MTFS-I is not designed to introduce frontline clinicians to new treatment approaches or core techniques.

### MTFS-I sustainability

Sustainability of innovations in behavioral treatment is an abiding concern of implementation science. MTFS-I procedures are sustainable beyond a research context only if (a) demands on provider time and resources are modest and (b) providers independently value its benefits and are motivated to utilize it. Regarding provider burden, MTFS-I is anchored by user-centered design features that minimize staff time commitments. The weekly time investment is 20 min for clinical staff for online training, plus another 15 min per week for therapists to enter ITT-ABP data and review feedback reports. These commitments appear feasible given the expected benefits of increased FBS quality. The flexibility of MTFS-I components also promotes their acceptability: Feedback report templates can be tailored to meet the needs of therapists, supervisors, administrators, and/or state agencies; and supervisors have appreciable latitude for how to incorporate report data into supervision meetings. The web-based learning management platform of MTFS-I is highly conducive to dynamic adaptation over time as procedures become routinized within a given agency. Finally, the proposed study is designed to test whether well-established innovation implementation strategies—core training and facilitation—enhance the sustainability of MTFS-I. Again, the time commitment for these quality procedures (six total hours for Core Training, followed weekly phone consultations and quarterly on-site meetings) seems quite favorable given the anticipated boost to the quality and maintenance of MTFS-I implementation.

Regarding provider motivation, there are several direct benefits and strong incentives for ASU treatment clinics to sustain MTFS-I. Our own research on EBIs for ASU in routine care [15–17, 26] has shown that clinicians are motivated to submit self-report data and engage in discussions related to quality improvement if they believe these activities enhance their clinical knowledge and skillsets and are valued by supervisors and agencies. Also, this study’s collaborative implementation activities will enable us to shape MTFS-I components according to local user needs [31]. These motivational processes can heighten provider commitment to adopting MTFS-I procedures, particularly when they are sanctioned by state regulatory agencies in support of government priorities for improved treatment quality and accountability. What is more, quality procedures grounded in pragmatic quality metrics such as the ITT-ABP will likely increase in value to treatment agencies as accountability contracting (e.g., value-based purchasing [66]) becomes commonplace. Finally, MTFS-I procedures bypass two major obstacles to implement MFS in routine behavioral care [35] by (a) providing ongoing and accessible training experiences to all system users and (b) ensuring that feedback data are systematically incorporated into everyday workflow and supervision.

## Abbreviations

ASU: Adolescent substance use
EBI: Evidence-based intervention
FBS: Family-based services
ITT-ABP: Inventory of Therapy Techniques for Adolescent Behavior Problems
MFS: Measurement feedback system
MTFS-I: Measurement Training and Feedback System for Implementation
